### Intervention description {11a}

Lithium salts such as lithium carbonate or citrate have been used for the treatment of bipolar disorder for decades for its mood stabilizing properties [9–11]. Within this population, lithium carbonate has been used effectively and safely with adequate monitoring. As such, its side-effects, both short- and long term, are well known. Given the fact that multiple trials with lithium carbonate have been performed in ALS, the side-effects of lithium carbonate in the target population of this study are also well known [14, 15, 20].

The study drug will be produced by TioFarma BV and is available as 400 mg capsules of lithium carbonate or matched placebo. Both the study drug and placebo are matched in appearance and packaging, and taken as capsules. Capsules will be taken once daily, starting with one capsule (400 mg daily) initially titrated up to two or three capsules daily over the first four weeks of treatment, depending on blood lithium levels. Blood levels will be measured at baseline, 7 days (12 h +/− 30 min after previous evening dose), and at 14 days (12 h +/−30 min after previous evening dose). The target range for the lithium plasma level will be between ≥0.4 mmol/l and ≤0.8 mmol/l. Further plasma level measurements will be taken at 21 and 28 days to confirm the target range has been achieved. Ongoing lithium level monitoring will be scheduled for week 8 and week 12, and quarterly thereafter for the duration of the study. Dose adjustments can be made by reducing back to 2 capsules daily or to 1 capsule daily as required. It is anticipated that most patients will remain on 2 capsules throughout the duration of the trial. Sham dose adjustments will also be made to patients on placebo to maintain blinding. Unused drug tablets and packaging will be returned during each visit.

Lithium plasma levels will be stored in the centralized online system (Research Online and Castor). Lithium plasma levels are sent to a dedicated mailbox for review by unblinded physicians. They will enter the new dose in the eCRF; subsequently the patient and the site staff will be notified. Study personnel should verify with the patient (by email or phone) that the dose adjustments resulting from the day 7 and day 28 lithium blood draw have been received and understood. On average the lithium levels will be stable after approximately three to four weeks (or 3–4 blood samples).

The Lithium Side Effects Rating Scale (LiSERS) will be used to monitor lithium use and flag potential lithium intoxications [21]. The LiSERS questionnaire may be completed by either the patient via email, or by study personnel via phone at days 7, 14, 21, 28, and 56 and after 3 months (within a 5-day window) since randomization. If lithium intoxication is suspected, the treating physician and/or unblinded physician are contacted to take appropriate action; dose-adjustments may be necessary.

### Criteria for discontinuing or modifying allocated interventions {11b}

Patients can withdraw from the trial at any time. Dose changes are made according to the plasma lithium levels which are determined regularly at the start of the trial. Furthermore, the LiSERS questionnaire will be used to monitor side effects and possible lithium intoxications which would warrant changes in dosage. In the exceptional case when plasma lithium levels exceed 0.8 mmol/l on two consecutive occasions while on the minimum dose of 1 capsule per day (400mg per day), this will be accepted if concentrations remain ≤1.0 mmol/l (for patients 65 years or older) or ≤1.5 mmol/l (for patients ≥18–<65 years). If values exceed these limits the investigational product must be permanently discontinued. Additionally, when patients display symptoms of a lithium intoxication (as evaluated by the unblinded physician and based on changes in LiSERS questionnaire outcome), the investigational product will also be permanently discontinued.

Interventions will not be withdrawn in case of worsening clinical condition due to ALS.

Patients will be withdrawn from the study by the Investigator in consultation with the coordinating Investigator and the Sponsor in case of:Liver toxicity where one or more of the following criteria (in alignment with the FDA premarketing clinical liver safety guidance) are met and no compelling alternate cause is):ALT ≥ 3×ULN and bilirubin ≥2×ULN (>35% direct bilirubin)ALT ≥ 5×ULNALT ≥ 3×ULN and with symptoms believed to be related to liver injury or hypersensitivity.ALT ≥ 3× baseline ALT and with symptoms believed to be related to liver injury or hypersensitivity.Allergic reaction criteria are met and no compelling alternate cause is identified:° CTCAE Grade III/IV: severe skin reaction (Steven-Johnson syndrome, Toxic Epidermal Necrolysis or Erythema Multiforme). Patients with Grade ≥3 allergic reactions that are considered to be possibly or probably related to the investigational product should permanently discontinue the investigational product regimen and the patient should be withdrawn from the study. Patients should be treated as clinically appropriate and followed until resolution of the adverse event.° Patients may continue investigational product for CTCAE Grade I or II allergic reactions at the discretion of the Investigator. The patient should be advised to contact the Investigator immediately if there is any worsening of symptoms or if further systemic signs or symptoms develop. Antihistamines, topical corticosteroids, or antipruritic agents may be prescribed.° If a profuse, purpuric and coalescing leukocytoclastic vasculitis occurs, the patient should be withdrawn from the study.Development of moderate to severe renal impairment as measured by Cystatin C (< 50 mL/min).Note: In case of renal impairment, medication may be stopped for 2 weeks, after which the patient is retested. If the renal impairments persist, patients are withdrawn from the study.The patient becomes pregnant.Noncompliance with the protocol as judged by the investigator.

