### Participant timeline {13}

The participant timeline can be seen in (Table 1). Study medication administration and concomitant medication or medical procedures are continuously recorded. Adverse events are continuously monitored and documented. Serious adverse events are continuously monitored and reported.

**Table 1 Tab1:** Participant timeline

	Screening (−45 days)	Baseline	Days 7, 14, 21, 28, and 56	Month 3 (±7 days)	Month 6 (±7 days)	Month 9 (±7 days)	Month 12 (±7 days)	Month 15 (±7 days)	Month 18 (±7 days)	Month 21 (±7 days)	Month 24 (±7 days)
Informed consent	X										
Eligibility criteria review	X	X									
DNA sample (10 mL)^a^	X										
Randomization		X									
Demographic data and medical history	X	X									
Neurological examination		X					X				X
12-lead ECG		X		X			X				X
Dispense study medication		X		X	X	X	X	X	X	X	
Drug accountability and compliance				X	X	X	X	X	X	X	X
Vital signs and body weight		X		X	X	X	X	X	X	X	X
Blood sample (30 ml)		X		X	X	X	X	X	X	X	X
Blood sample (lithium level)			X	X	X	X	X	X	X	X	X
Urine sample (20 ml)		X		X	X	X	X	X	X	X	X
Pregnancy test^b^	*For WOCBP patients: at a monthly interval*										
Spirometry (SVC)	X	X		X	X	X	X	X	X	X	X
ALSFRS-R	X	X		X	X	X	X	X	X	X	X
Quality of life (VAS and EQ-5D)		X		X	X	X	X	X	X	X	X
LiSERS questionnaire			X	X							
King’s staging system		X		X	X	X	X	X	X	X	X
ECAS		X					X				X
ALS-FTD-Q		X					X				X
Optional: liquor biomarker sample		X			X		X				
Optional: CMAP scan^c^		X		X	X	X	X				
Survival data and ALS interventions^d^	X	X		X	X	X	X	X	X	X	X

^a^End-of-Study or early-termination visit

^b^Pregnancy tests can be performed by the patient themselves at home

^c^CMAP scan is only performed in the UMC Utrecht

^d^ALS interventions are gastrostomy, non-invasive ventilation, wheelchair use and tracheostomy

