## Assignment of interventions: blinding

### Who will be blinded {17a}

All staff, patients and personnel involved with the study will be masked to treatment, except site pharmacy personnel and the unblinded physicians. Furthermore, at least one sponsor safety employee will be unblinded in the case of serious safety events requiring unmasking. Information on lithium plasma levels is only accessible by the unblinded physicians. Lithium plasma levels will not be reported in (electronic) patient records.

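### A permanent stop rests partly on changes in LiSERS, but the first LiSERS comes at day 7 on study drug: one pre-dose score at baseline would be a cheap improvement (minor, safety only)

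*Protocol article*

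**What the plan says.** Section {11b} of the protocol article gives LiSERS two uses. For dosing, "the LiSERS questionnaire will be used to monitor side effects and possible lithium intoxications which would warrant changes in dosage". For stopping, a patient with symptoms of intoxication is assessed "as evaluated by the unblinded physician and based on changes in LiSERS questionnaire outcome), the investigational product will also be permanently discontinued". The same section adds that worsening of the ALS itself is no reason to withdraw treatment.

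Section {11a} sets the LiSERS schedule: "at days 7, 14, 21, 28, and 56 and after 3 months (within a 5-day window) since randomization". In Table 1 (Participant timeline {13}), the row "LiSERS questionnaire" is marked under the day 7 to 56 column and month 3 only. It is blank at screening, at baseline and from month 6 on. Dosing begins before the first of these scores, "starting with one capsule (400 mg daily) initially titrated up to two or three capsules daily over the first four weeks of treatment".

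**The concern.** A rule that uses change needs a reference value. Here the earliest value is taken after about a week on study drug. A complaint that began in that week is already part of the reference. A complaint present before lithium looks the same in the scores. In ALS the distinction matters, because patients bring symptoms of their own disease and {11b} does not allow those to trigger withdrawal.

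At stake is the basis for an irreversible treatment stop in individual patients, and for some dose changes. Time to discontinuation of assigned treatment is also the tolerability outcome (Outcomes {12}), so the rule touches a reported secondary result. It does not touch the primary endpoint.

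**Working it through.** No figure in the plan needs reproducing. The check sets the rule beside the schedule.

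**1. Count the scores.** Section {11a} and Table 1 both give days 7, 14, 21, 28 and 56 plus month 3, so 5 + 1 = 6. Pre-dose scores: 0. Text and table agree, so this is not a damaged table row.

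**2. Count the changes that can be read.** Six serial scores give 6 − 1 = 5 consecutive changes, all between scores on study drug. At day 7 there is no earlier score, so no change exists. Day 7 is also the time of a lithium draw from which {11a} expects dose adjustments.

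**3. See which complaints the reference can separate.** Take three complaints that persist once present, and assume that the items record current symptoms without asking when they began (the article does not reproduce the scale).

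| Complaint | Pre-dose | Day 7 | Day 14 | Change from day 7 | Change from pre-dose, at day 7 / day 14 |
|---|---|---|---|---|---|
| Present before lithium | yes | yes | yes | none | none / none |
| Begins in week 1 | no | yes | yes | none | rise / rise |
| Begins in week 2 | no | no | yes | rise | none / rise |

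With day 7 as the reference, the first two rows cannot be told apart. With a pre-dose score they can. The third row is detected either way. The loss is therefore limited to complaints that start in the first week and to complaints that were there already.

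**4. Compare with another rule in the same section.** One liver criterion in {11b} is set at three times "baseline ALT and with symptoms believed to be related to liver injury or hypersensitivity". There a pre-treatment reference is named.

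**5. Count the effect of the fix.** One baseline score gives 6 + 1 = 7 LiSERS per patient. All 6 existing scores, instead of none, can then be compared with a pre-dose value.

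**The case against.** The strongest reply is that nothing is contradicted. Section {11b} speaks of changes, not of change from baseline, and the authors name baseline where they mean it, as in the ALT criterion and in several secondary outcomes. That stands: the ALT criterion shows what a pre-treatment reference looks like, not that the LiSERS rule promised one.

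It also stands that day 7 is a usable reference for much of the purpose. It falls at the lowest dose, before most of the titration, so toxicity from later escalation would show as a rise. LiSERS is one input and not a numeric threshold. The decision lies with the unblinded physician, who also sees the lithium levels: "Information on lithium plasma levels is only accessible by the unblinded physicians". Baseline history and a baseline neurological examination are in Table 1.

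A reader might infer two stronger points, and neither is supported.

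- *Toxicity goes unwatched after month 3, because the stopping rule has no time limit but LiSERS ends.* Section {22} describes LiSERS as a tool for the start of treatment, so its end at month 3 is a chosen scope. Quarterly lithium levels, the separate plasma-level stop, the Cystatin C criterion and adverse-event inquiry at each visit all continue. Clinicians can act on suspicion at any time: "If lithium intoxication is suspected, the treating physician and/or unblinded physician are contacted to take appropriate action; dose-adjustments may be necessary". Whether LiSERS is repeated on suspicion may be set out in the full protocol.
- *The stopping rule cannot be applied.* It can, through serial scores, plasma levels and clinical judgment.

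What the reply does not remove is that the scores cannot show the state before lithium.

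**Conclusion.** The point holds as a minor, optional safety improvement. As scheduled, 0 of 6 LiSERS scores precede the first dose, so a named input to a permanent stop can be read only against values on study drug.

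This rests on two assumptions. The first is that dosing starts at or soon after the baseline visit, where Table 1 places both randomization and dispensing. The second is that LiSERS items describe current symptoms; if the scale itself asks about onset, less is lost. The schedule counts are certain. The size of the benefit is not: the documents give no figure for how many stopping or dosing decisions would change, and none is claimed. The primary analysis, number of events, sample size and power are unaffected.

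**What to change.** Mark LiSERS at the baseline visit in Table 1, to be completed before the first dose, for patients not yet randomized. Add one sentence to {11b}: change in LiSERS is judged against the pre-dose score or, for patients already randomized, against day 7. No LiSERS needs to be added after month 3.

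The cost is one table mark, one sentence and one short questionnaire per patient (7 instead of 6) at a visit that already takes place. Recruitment began in August 2021, so two kinds of reference will exist, pre-dose and day 7, for patients enrolled after and before the change. Any description of LiSERS-based stops should say which one applied.

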### Outcomes {12}

#### Primary outcomes

The primary endpoint of this study is a composite endpoint, defined as time to death from any cause or respiratory insufficiency (tracheostomy or the use of non-invasive ventilation for ≥22 h per day for ≥10 consecutive days).

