### Plans to promote participant retention and complete follow-up {18b}

As ALS progresses, patients may experience increasing difficulty to adhere to the nominal visiting schedule. To reduce discontinuations due to non-compliance, we provide an alternative monitoring option for debilitated patients, if allowed according to local laws and regulations. If, in the judgment of the principal investigator, the patient cannot reasonably be expected to travel to the clinic, the minimum data required for continued participation in the study (i.e., remain on the study medication) are laboratory tests, adverse event reporting and ALSFRS-R, all of which can be obtained remotely by a trial nurse, either during a home visit or by phone. Blood samples for safety assessments may be obtained by the patient’s general practitioner or any other local blood collection option that has been approved by the Sponsor. These data are to be obtained according to the nominal visit schedule until the patients withdraws, reaches the endpoint or the study completes, whichever comes first. If the patient becomes unfit for travel, this information will be documented in the source data. If no accommodations can be made for adequate safety monitoring, patients are withdrawn from study medication and the minimum requirement for follow-up will be assessment of survival data (i.e., living status or date of death).

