#### Analysis populations

*The efficacy population* will be used for the primary efficacy analysis. The efficacy population includes all randomized patients irrespective of follow-up or receiving the actual study medication (intention-to-treat). Patients will be analyzed according to their randomization assignment.*The safety population* will consist of all randomized patients who received at least one dose or portion of a dose of study medication. Patients will be analyzed according to the treatment they received.

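### Section {11b} withdraws some patients from the study and not only from the drug, with no stated follow-up for the primary endpoint, against the intention-to-treat analysis

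*Protocol article*

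**What the plan says.** The primary endpoint (Primary outcomes) is "time to death from any cause or respiratory insufficiency", the latter meaning tracheostomy or NIV at 22 hours a day or more for ten or more days in a row. Under Analysis populations: "The efficacy population includes all randomized patients irrespective of follow-up or receiving the actual study medication (intention-to-treat". Section {20c} rules out imputing any outcome.

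Section {11b} lists grounds for leaving the trial: "Patients will be withdrawn from the study by the Investigator in consultation with the coordinating Investigator and the Sponsor in case of" liver toxicity, allergic reaction and the other triggers. For Grade 3 or higher related allergic reactions, patients "should permanently discontinue the investigational product regimen and the patient should be withdrawn from the study". A severe vasculitis also ends study participation. For the kidney: "If the renal impairments persist, patients are withdrawn from the study". The list closes with "The patient becomes pregnant" and "Noncompliance with the protocol as judged by the investigator".

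Elsewhere only the drug stops. Earlier in {11b}, lithium levels above the stated limits and symptoms of lithium intoxication end the product. In {11d}, starting edaravone ends study treatment.

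Section {18b} has a remote option for patients who cannot travel. If safety monitoring cannot be arranged even then, they come off the drug and "the minimum requirement for follow-up will be assessment of survival data (i.e., living status or date of death".

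**The concern.** An intention-to-treat analysis of a time-to-event endpoint needs the events that occur after a patient stops the drug. Keeping withdrawn patients in the denominator does not supply those events: if follow-up ends, they are censored on the day they leave. Several exits in {11b} could be drug effects (liver, allergy, kidney). Noncompliance may be related to prognosis: {18b} itself says that patients find the visit schedule harder to keep as ALS progresses. Censoring could therefore depend both on arm and on risk, which a stratified or covariate-adjusted likelihood ratio test does not fully remove.

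A second, smaller gap lies in {18b}. Living status or date of death supplies one half of the composite. A patient followed only at that minimum who reaches tracheostomy or the NIV threshold is either missed or counted later, at death.

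At stake are the hazard ratio of a confirmatory trial planned on 72 events and, to a lesser degree, the time to reach those events. Endpoint dates not collected at the time may not be recoverable later.

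**Working it through.** **1. Is leaving the study a separate act from stopping the drug?** Yes, on three readings of the article. For Grade 3 or higher related allergic reactions {11b} orders both acts in one sentence. Section {20a} summarises premature discontinuation of treatment and of the study separately. High lithium levels, intoxication and edaravone use the drug-stop wording alone. So the study-withdrawal wording is not simply a loose way of saying that the drug stops.

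**2. Does any section follow these patients afterwards?** Table 1 schedules survival data and ALS interventions (including NIV and tracheostomy) at every quarterly visit, but for patients still in the study. The off-drug survival follow-up in {18b} covers only patients unfit to travel whose safety monitoring cannot be arranged. No section shown covers the {11b} withdrawals.

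**3. The plan's own figure.** Inputs from Sample size {14}: HR 0.50, one-sided alpha 0.025, 80% power, 2:1 allocation.

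Events = (1.960 + 0.842)² / [(2/3)(1/3)(ln 0.5)²] = 7.85 / (0.2222 × 0.4805) = 73.5, so 74, against the stated 72. Power at 72 events = Φ(√(72 × 0.1068) − 1.960) = Φ(0.813) = 79.2%; with the Table 2 bounds it is 78.2%. The plan's figure is reproduced closely enough.

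**4. Effect on the hazard ratio (assumed rates).** Very large simulated trials (900,000 patients, 2:1): exponential events, placebo median 14.5 months, 24 months of follow-up. A latent share of patients has hazard k times that of the rest. On lithium all of this share withdraw; on placebo only some do. Withdrawal times are uniform over the first 12 months. True HR 1.00; each cell gives the estimate with full follow-up, then with censoring at withdrawal.

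| Withdrawal, lithium/placebo | k = 1 | k = 1.5 | k = 2 | k = 3 |
|---|---|---|---|---|
| 5%/2% | 1.002, 1.001 | 0.998, 0.991 | 1.000, 0.989 | 0.997, 0.984 |
| 10%/5% | 1.003, 1.003 | 0.998, 0.985 | 1.001, 0.983 | 1.002, 0.981 |
| 15%/5% | 0.999, 0.999 | 1.001, 0.978 | 0.999, 0.965 | 0.998, 0.957 |

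With a true HR of 0.50 within risk class and 15%/5%, the estimate moves from 0.503 to 0.488 (k = 1.5) and from 0.521 to 0.482 (k = 3).

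**5. What that means for the test.** At 72 events and 2:1, SE(log HR) = 1/√(72 × 2/9) = 0.25. An HR of 0.98 is |ln 0.98|/0.25 = 0.08 SE, so a nominal one-sided 2.5% becomes about 1 − Φ(1.96 − 0.08) = 3.0%. The worst cell, 0.957, is 0.18 SE, giving about 1 − Φ(1.78) = 3.7%. Both use a fixed design without covariate adjustment.

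**6. Effect on event numbers.** Assumptions: HR 0.50, accrual 5.5 per month, at most 24 months per patient, cut at 48 months. Placebo medians of 14 and 14.5 months give 99.8% and 99.3% of trials reaching 72 events, around the stated 99.5%. At 14.5 months, with withdrawal unrelated to prognosis and rates by 24 months:

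| Withdrawal, lithium/placebo | Mean events | Reach 72 |
|---|---|---|
| none | 86.7 | 99.3% |
| 5%/2% | 85.2 | 98.2% |
| 10%/5% | 83.6 | 96.9% |
| 15%/5% | 82.7 | 96.6% |
| 20%/10% | 80.8 | 92.9% |

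A shortfall costs some power: by the formula in step 3, 76.9% at 68 events and 75.0% at 65.

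**The case against.** The best counter-argument is that loss of follow-up is inferred from silence. The article never says that vital status is not collected after withdrawal, and the full protocol may provide for it. This stands as a limit on confidence. It does not remove the point, because the article states study withdrawal as a positive rule, and a follow-up clause elsewhere would have to be reconciled with it.

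Four stronger readings are tempting and are not supported.

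- A reader might take the sentence in {18b} about collecting data until withdrawal as ending all data collection. It governs the remote-monitoring minimum (laboratory tests, adverse events, ALSFRS-R) for patients who cannot travel.
- A reader might conclude that every off-drug patient is followed for death alone. The survival-only floor covers only the subset whose safety monitoring cannot be arranged.
- A reader might conclude that lithium toxicity in general removes patients from the study. Intoxication and excess levels stop only the product.
- A reader might assume that missed respiratory events favour lithium. The trigger in {18b} is disability. If lithium works, placebo patients could reach it sooner and the bias could run against lithium.

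It is also fair that the eligibility window on the TRICALS risk profile and adjustment for it would absorb part of any link between withdrawal and prognosis, which the simulation ignores. The by-arm summaries in {20a} would show an imbalance, though they would not repair it.

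**Conclusion.** The point holds as a conflict between the study-withdrawal rule in {11b} and the intention-to-treat primary analysis, and as an inconsistency with the drug-only stops in {11b} and {11d}. The gap in {18b} is real but narrow, and the sign of its effect is undetermined.

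The likely size is modest. At 5%/2% and 10%/5% the shift is about 0.01 to 0.02 on a hazard ratio of 1.00; at 15%/5% it is about 0.02 to 0.04. It is zero if withdrawers have average prognosis. These figures rest on assumed rates, on more withdrawal on lithium, and on withdrawers being at higher risk; the documents establish none of the three. The Discussion reports one earlier lithium trial in ALS stopped over extensive discontinuation, but also later placebo-controlled trials without major safety concerns. Larger shifts, to about 0.92 to 0.96, appear only if 20% to 30% of lithium patients are assumed to withdraw within 12 months (against 5% to 10% on placebo), which nothing in the article supports for these triggers. Loss of events is a minor matter at modest rates, because the design expects more than 72.

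This should be fixed, with medium confidence because the full protocol is not shown.

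**What to change.** Leave every criterion for stopping the drug as it is. In {11b}, separate stopping study medication from leaving the study. State that all randomized patients, on or off drug, are followed for death and respiratory insufficiency until the event, withdrawal of consent to follow-up, or the end of the trial. In {18b}, add to the survival minimum the date of tracheostomy and the date on which the protocol's NIV criterion is met; both can be asked by phone. If the full protocol already provides this follow-up, the wording of {11b} and {18b} should be reconciled with it.

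The cost is protocol wording and a few more calls per site, for example quarterly, with no added procedure. The planned 72 events and 80% power are unchanged.
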